### Statistical analysis

Normally distributed continuous variables will be presented as mean ± standard deviation (SD), non-normally distributed variables as median (interquartile range, IQR) and categorical variables as number (percentage).

For outcomes assessed at multiple time points, a linear mixed model for repeated measurements (MMRM) will be employed, with fixed effects including group, time point and the group × time interaction, patient as a random intercept, and pairwise comparisons between groups adjusted using Tukey’s correction. Missing data in repeated-measures analyses will be handled under the assumption of missing at random (MAR) using maximum likelihood estimation. The MMRM model naturally accommodates missing data without pre-imputation. A sensitivity analysis using multiple imputation will be conducted to test the robustness of results.

For single time point analyses, normally distributed continuous variables will be compared using one-way ANOVA, followed by post‑hoc pairwise comparisons with Tukey’s correction; non-normally distributed variables using the Kruskal‑Wallis test; and categorical variables using the chi‑square test or Fisher’s exact test as appropriate. Multivariable linear regression will be used to adjust for potential confounding factors, including age, sex, body mass index (BMI), baseline NRS score and surgical duration. A two-sided *P* value < 0.05 will be considered statistically significant.

For the trial to be declared positive regarding the primary hypothesis, both co-primary endpoints must reach statistical significance. Specifically, for at least one pairwise comparison, a statistically significant difference must be observed in both the 48-hour resting pain NRS score and the cumulative 0–48 h MME consumption, after applying Tukey’s correction for multiple comparisons within each endpoint. No additional alpha adjustment (e.g. Bonferroni) will be applied across the two co-primary endpoints. According to ICH E9 guidelines for co-primary endpoints, when a trial requires statistical significance on all co-primary endpoints to declare a positive result, the family-wise error rate is inherently controlled without further adjustment. This principle applies here, as both endpoints must demonstrate improvement to define a clinically successful analgesic regimen.

The primary analysis will follow the intention-to-treat (ITT) principle. The ITT population includes all randomized patients who received the study intervention and had at least one post-baseline outcome assessment. As a supportive analysis, a per-protocol (PP) sensitivity analysis will be performed to assess the robustness of the findings. The PP population includes patients without major protocol deviations.

Statistical analyses will be conducted using the SPSS 20.0 software (IBM SPSS, Chicago, IL, USA).

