### Primary and secondary outcomes

The co-primary outcomes will be (1) Rest pain NRS score at 48 h post‑surgery; (2) Cumulative opioid consumption within 0–48 h after surgery, converted to oral morphine milligram equivalents (MME). Secondary outcomes will be (1) Rest pain NRS scores at 6 h, 24 h and 72 h post‑surgery; (2) Muscle Balance Scale (MBS) ratings at 6 h, 24 h, 48 h and 72 h; (3) Motor nerve block assessed by the Bromage score at 6 h, 24 h, 48 h and 72 h [23]; (4) American Shoulder and Elbow Surgeons (ASES) functional score at the same intervals (Table 1); (5) Quality of Recovery-15 (QoR-15) score at 24 h and 48 h post‑surgery.

**Table 1. t0001:** The American shoulder and elbow surgeons (ASES) score.

Activity	Unable to do Score = 0	Very difficult to do Score = 1	Somewhat difficult Score = 2	Not difficult Score = 3
Do usual work				
Do usual sport				
Put on a coat				
Sleep on your painful or affected side				
Wash back/do up bra in back				
Manage toileting				
Comb hair				
Reach a high shelf				
Lift 4.5kg above shoulder				
Throw a ball overhand				
Total scores				

A patient-reported subjective rating system was employed to assess the score, comprising two components: pain (50%) and functional capacity (50%), with a total possible score of 100. Higher scores indicate superior shoulder function.

Specific scoring method: pain score = (10-NRS score) *5; Functional score = total score of 10 items *5/3.

ASES score = pain score + function score.

Although liposomal bupivacaine provides analgesia lasting up to 72 h, its most stable and clinically consistent effect occurs within the first 48 h after surgery. This period also represents the critical window for early postoperative rehabilitation, opioid consumption and acute pain control. Therefore, 48 h was selected as the primary time point to capture the most clinically meaningful analgesic difference among groups, while 72 h was retained as a secondary outcome to assess the extended duration of action.

NRS scores range from 0 (no pain) to 10 (worst imaginable pain). Mild pain (1–3) is non‑disruptive to sleep, moderate pain (4–6) mildly disrupts sleep and severe pain (7–9) prevents or awakens from sleep.

The MBS assesses elbow and wrist flexion strength using a 5‑point scale: 0 (no muscle activity), 1 (slight movement), 2 (movement against gravity only), 3 (movement against resistance with reduced strength) and 4 (strong movement against resistance).

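### The only within-patient structure stated for the 48 h NRS co-primary is a random intercept, and no single primary test is named; the 48 h standard error may rest on a variance averaged over four visits

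*Protocol article*

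**What the plan says.** Primary and secondary outcomes: "The co-primary outcomes will be (1) Rest pain NRS score at 48 h" after surgery, together with cumulative MME over 0–48 h. The secondary list adds "Rest pain NRS scores at 6 h, 24 h and 72 h", so the same scale is recorded at four visits, as Table 3 confirms.

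Statistical analysis offers two routes that could apply to the 48 h value:

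- "For outcomes assessed at multiple time points, a linear mixed model for repeated measurements (MMRM) will be employed", with group, time and their interaction as fixed effects, and with "patient as a random intercept, and pairwise comparisons between groups adjusted using" Tukey's method. No residual covariance and no visit-specific variance is stated.
- "For single time point analyses, normally distributed continuous variables will be compared using one-way ANOVA" with Tukey comparisons, or Kruskal-Wallis if the data are not normal.

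No sentence assigns the 48 h NRS to either route. A two-sided P "value < 0.05 will be considered statistically significant". Success requires at least one pair of groups to differ significantly on both co-primaries, with Tukey's correction inside each. On that basis the section states that "the family-wise error rate is inherently controlled without further adjustment".

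**The concern.** An MMRM ordinarily lets each visit have its own variance and each pair of visits its own correlation. A patient random intercept with independent, equal-variance residuals does not: it implies one variance and one correlation for all visits. The label and the stated structure therefore disagree. The variance that matters for the co-primary is the one at 48 h, and the stated structure would estimate it from 6, 24 and 72 h as well.

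The level of a co-primary test is at stake. Requiring significance on both endpoints removes the need for a further alpha split only if each component test holds its own level. If MME truly differs between groups, as the plan expects, the MME requirement is nearly always met, and the trial's false-positive rate becomes that of the NRS test. The open choice between two tests with different standard errors adds a second difficulty, since the result could depend on which is reported.

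**Working it through.** **Inputs from the protocol article.** Four NRS visits (6, 24, 48 and 72 h); three groups; Tukey; alpha 0.05 two-sided; 84 evaluable per group; MME means 20, 35 and 50 mg with SD 12. The NRS SDs used below are assumptions, because the article gives none.

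**The plan's own figure.** The article gives no NRS standard error to reproduce. Its sample size of 84 is close to a two-group comparison of 15% with 35% at 80% power and alpha 0.05 with continuity correction, which gives 83. Dropout: 84 / 0.90 = 93.3, rounded up to 94, and 3 × 94 = 282, as stated. I use 84 per group below.

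**Variance used by the random-intercept model.** With complete balanced data, let Σ be the true 4 × 4 covariance of the visits.

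- Expected between-patient mean square: MSB = 1′Σ1 / 4
- Expected within-patient mean square: MSW = (trace Σ − 1′Σ1 / 4) / 3
- Model variance at every visit: (MSB + 3 × MSW) / 4 = trace Σ / 4

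The correlation terms cancel. The model variance at 48 h is the mean of the four visit variances. Group × time is in the model, so the estimated 48 h group means are the raw means, and only their standard error is affected.

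**Effect on Tukey error.** Put r = SD at 48 h / root-mean-square SD over the four visits. The model standard error is 1/r times the correct one, so

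family-wise error = P(Q₃ > q₀.₉₅ / r),

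where Q₃ is the studentised range of three means.

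| r | 0.8 | 0.9 | 1.0 | 1.1 | 1.2 | 1.3 |
|---|---|---|---|---|---|---|
| Error | 1.0% | 2.5% | 5.0% | 8.4% | 12.4% | 16.8% |

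**Worked example.** SDs 1, 1.5, 2, 2 at 6, 24, 48, 72 h: mean variance (1 + 2.25 + 4 + 4) / 4 = 2.8125; root-mean-square SD 1.677; r = 2 / 1.677 = 1.193; error 12.1%.

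**Simulation of the whole success rule.** 84 per group, 20,000 trials per row, no true NRS difference, MME at the planned means, within-patient correlation 0.5:

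| Assumed SDs (6/24/48/72 h) | r | Random intercept | 48 h variance only |
|---|---|---|---|
| 2 / 2 / 2 / 2 | 1.00 | 5.0% | 4.9% |
| 1 / 1.5 / 2 / 2 | 1.19 | 12.1% | 5.0% |
| 1.5 / 2 / 2.5 / 2 | 1.23 | 13.8% | 4.9% |
| 1 / 1.8 / 1.6 / 1.4 | 1.08 | 7.9% | 5.2% |
| 2.5 / 2.5 / 2 / 1.5 | 0.92 | 3.1% | 5.1% |
| 2.5 / 2 / 1.5 / 1 | 0.82 | 1.2% | 4.9% |
| 1 / 2 / 2 / 2.65 | 1.00 | 4.8% | 4.7% |

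Simulation error is about 0.15 percentage points. The last row shows that unequal variances alone do no harm if the 48 h variance happens to equal the four-visit mean: (1 + 4 + 4 + 7) / 4 = 4 = 2².

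**Correlation pattern.** With equal SDs and AR(1) correlation 0.7, the two methods gave 5.3% and 5.4%. The visit variances drive the effect here, not the correlation shape.

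**Why the MME requirement does not protect.** At the planned values the smallest MME difference is 15 mg with standard error 12 × √(2/84) = 1.85, a ratio of 8.1 against a Tukey threshold of 3.334 / √2 = 2.36. MME is then significant for every pair almost always. If MME is also null, the rule's error is only 0.2% even with SDs 1, 1.5, 2, 2.

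**The case against.** Four objections deserve weight.

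*The 48 h NRS may go to ANOVA.* The co-primary is defined at one time point, the other NRS visits are listed separately as secondary, and one-way ANOVA with Tukey fits the wording of the success rule. On that route the standard error is the 48 h one and the variance problem disappears. This stands: a reader might infer that the random-intercept test is settled, and the article does not support that. Yet NRS is plainly an outcome assessed at multiple times, and the article leaves both routes open.

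*A random intercept need not mean one variance.* Visit-specific residual variances could be added, and an unseen analysis plan may do so. This stands as a condition on the numbers. It does not remove the point, because the random intercept is what the article affirmatively states and it does not match the MMRM label.

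*The size is assumed.* A reader might infer that the false-positive rate is inflated, or that it is wrong unless pain varies equally at every visit. Neither follows. No NRS SDs are given, the error can fall as well as rise, and the 48 h variance need only equal the four-visit mean. Nor does the rationale for choosing 48 h in Primary and secondary outcomes say anything about spread between patients.

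*The error-control statement concerns multiplicity across the two endpoints.* That reasoning is sound as far as it goes. A reader might infer that it fails outright. It fails only if the NRS test is off its level, and in the anti-conservative direction, while MME truly differs.

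**Conclusion.** The point holds in conditional form and is of moderate severity. The article does not name one primary test for the 48 h NRS. The route that applies on the plain reading states a structure that, with homogeneous residuals, replaces the 48 h variance by the four-visit average. For r from 0.8 to 1.3, Tukey family-wise error is about 1% to 17% against 5%; even mild heterogeneity such as SDs 1.8, 1.9, 2.0, 1.9 (r = 1.05) gives 6.6%. Below r = 1 the cost is lost power instead.

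The figures assume complete data, 84 per group, normal scores and SDs chosen for illustration. Neither the presence nor the direction of a bias in this trial can be established from the article. A 48 h-specific variance keeps the error at 4.7% to 5.4% in every scenario tried, so the question need not be left to chance.

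**What to change.** In Statistical analysis, replace the patient random intercept with an unstructured within-patient covariance over 6, 24, 48 and 72 h, fitted by REML, with Satterthwaite or Kenward-Roger degrees of freedom where the software supports them. Name the Tukey-adjusted 48 h group contrasts from that model as the single co-primary NRS test. Confine the ANOVA and Kruskal-Wallis sentence to outcomes measured once, such as MME, or label any such 48 h NRS analysis as supportive.

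Naming the 48 h ANOVA instead would also give a correct standard error. The unstructured model fits better with the article's own likelihood-based handling of missing data.

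The cost is one or two sentences and 4 × 5 / 2 = 10 covariance parameters, estimated from roughly 252 (3 × 84) to 282 patients. No change to the sample size or data collection is needed. It should be settled before outcome data are analysed.

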### Study interventions

A single ultrasound-guided STB will be administered in the pre-anaesthesia room 1 hour preoperatively. The STB procedure will be performed by a qualified anaesthesiologist under sterile conditions. The patient will be placed in the supine position with the head turned slightly to the contralateral side. A high-frequency linear ultrasound transducer (6–13 MHz) will be positioned in the supraclavicular fossa with a transverse oblique orientation. The brachial plexus will be identified, and the superior trunk (formed by the C5 and C6 nerve roots) will be visualized as a hypoechoic structure lateral to the subclavian artery. A 22-gauge, 50-mm echogenic needle will be inserted using an in-plane approach from lateral to medial, with the needle tip placed adjacent to the superior trunk. Following negative aspiration, the assigned dose of liposomal bupivacaine (66, 44 or 33 mg) will be diluted with normal saline to a total volume of 10 mL and injected in 2–3 mL aliquots under real-time ultrasound guidance to ensure proper spread. Block success will be confirmed 15 min after injection by assessing sensory loss (cold test) and motor weakness (reduced strength of deltoid and biceps muscles) compared with the contralateral side. Following the block procedure, patients will undergo continuous electrocardiogram (ECG) monitoring for 1 hour to enable immediate management of any serious adverse events. Known side effects of STB include nausea, vomiting, constipation, tachycardia, bradycardia, dizziness, headache, somnolence and hypoesthesia. The most serious risk is arrhythmia due to inadvertent intravascular injection, which ultrasound guidance helps to mitigate. Mild adverse events will not require treatment; moderate-to-severe events will receive appropriate pharmacologic intervention. If a severe event occurs after 50% of the dose has been administered, the injection will be discontinued immediately. Acute allergic reactions will be managed according to standard institutional protocols. All adverse events will be fully documented in the case report form.

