## Discussion

This study investigates the optimization of regional analgesia within ERAS protocols for shoulder arthroscopy, focusing on the balance between prolonged pain control and functional recovery. The shift from the traditional ISB to the STB is primarily motivated by the imperative to reduce iatrogenic morbidity, specifically HDP. By selectively targeting the superior trunk, STB significantly mitigates the risk of phrenic nerve palsy [17–20], enhancing patient safety-a cornerstone of the ERAS philosophy. This safety profile makes STB particularly advantageous for patients with pre-existing pulmonary compromise.

The incorporation of liposomal bupivacaine addresses the well-documented limitation of short-lived analgesia from single-injection nerve blocks. Its sustained-release formulation has demonstrated superiority over conventional local anaesthetics in providing pain relief during the critical 24 to 48-hour postoperative window and in reducing opioid requirements [14–16]. However, its extended duration of action presents a unique challenge in the context of peripheral nerve blocks: the potential for disproportionately long-lasting motor blockade. In shoulder surgery, where early passive and active motion is crucial for recovery, prolonged motor weakness could paradoxically impede rehabilitation progress and patient satisfaction, counteracting ERAS goals.

Existing literature offers limited guidance on employing liposomal bupivacaine in the STB approach. While its efficacy in ISB is established [14–16], the pharmacokinetics and optimal dosing for the more focused STB technique require dedicated evaluation. The central question is not merely whether it works, but at what concentration it provides an optimal sensory-motor dissociation – sufficient analgesia without undue motor impairment. This study directly addresses this gap by systematically evaluating different concentrations to define this therapeutic window.

The clinical implications of defining an optimal concentration are substantial. A successful regimen would yield a multimodal analgesic strategy that synergizes safety (low HDP risk of STB), efficacy (prolonged analgesia from liposomal bupivacaine) and functionality (preserved motor function for early mobilization). This aligns perfectly with the holistic aims of ERAS, potentially improving recovery quality, reducing opioid-related side effects and increasing patient satisfaction after shoulder arthroscopy.

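### The random-intercept model gives the 0–4 motor grade one variance at all four times; if most patients are back at grade 4 by 72 h, uncommon residual block will often be missed

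*Protocol article*

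**What the plan says.** The Statistical analysis section of the protocol article states: "For outcomes assessed at multiple time points, a linear mixed model for repeated measurements (MMRM) will be employed". Its fixed effects are group, time and their interaction, with "patient as a random intercept, and pairwise comparisons between groups" adjusted by Tukey's method. No other covariance structure is mentioned. Rank and categorical tests are reserved for single-time analyses. The named sensitivity analyses, multiple imputation and per-protocol, leave the variance assumption unchanged.

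Primary and secondary outcomes lists "Muscle Balance Scale (MBS) ratings at 6 h, 24 h, 48 h and 72 h", graded 0 (no muscle activity) to 4 (strong movement against resistance), so MBS falls under this model. So does the Bromage score at the same times. Its range is not given, and no figures are claimed for it.

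**The concern.** A patient random intercept with an ordinary residual gives the same total variance at every visit, and hence the same standard error for every between-arm contrast. A grade that recovers towards a ceiling cannot be expected to behave like that. The block is confirmed by "motor weakness (reduced strength of deltoid and biceps muscles) compared with the contralateral side" (Study interventions), and of the drug's analgesia the article says "its most stable and clinically consistent effect occurs within the first 48 h after surgery" (Primary and secondary outcomes). Many patients may therefore be at grade 4 by 72 h, with little spread left.

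The pooled variance would then be too large at 72 h and too small at whichever earlier time has the widest spread. That is 6 h if early block is partial, and 24 or 48 h if it is dense at 6 h.

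The trial seeks a dose giving "sufficient analgesia without undue motor impairment", and the Discussion names "the potential for disproportionately long-lasting motor blockade" as the particular risk of this drug. Real late weakness could be reported as non-significant, and arms of equal strength could be called different too often at an earlier time.

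**Working it through.** **Inputs.** From the article: 84 evaluable per arm (94 enrolled, 10% dropout), three arms, two-sided 5%, Tukey over three pairs. It gives no power figure for MBS to reproduce and no grade distributions. Everything below about grades is therefore assumed, over a range of patterns.

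Assumed probabilities of grades 0/1/2/3/4 at 6 h; 24 h; 48 h:
- Marked: .15/.25/.30/.20/.10; .05/.15/.25/.30/.25; .01/.04/.10/.25/.60
- Mild: .02/.06/.12/.30/.50; .01/.03/.08/.23/.65; .005/.015/.05/.13/.80
- Very mild: .005/.02/.06/.215/.70; .003/.012/.04/.145/.80; .001/.009/.03/.06/.90
- Dense, 50% at grade 0: .50/.30/.15/.04/.01; .20/.25/.25/.20/.10; .05/.10/.20/.30/.35
- Dense, 60%: .60/.25/.10/.04/.01; .25/.25/.25/.15/.10; 48 h as for 50%
- Dense, 80%: .80/.15/.04/.01/0; .35/.25/.20/.12/.08; .10/.15/.20/.25/.30

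At 72 h a fraction r is below grade 4, split 10/30/60% over grades 1/2/3. Arm B lies midway between A and C. Arms are equal before 72 h, and the within-patient latent correlation is 0.5.

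**Standard errors.** With complete data:
- stated model: SE = √(2 × mean of the four variances / n), which matched a REML fit in a test case (0.1598 by both routes);
- time-specific variance: SE = √(2 × variance at that time / n).

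**Worked case: marked block, 15% (A) versus 3% (C) at 72 h.**
1. Shortfalls from grade 4 are 3, 2 and 1, so the mean shortfall is 1.5r and the variance is 2.7r − 2.25r². For r = 15%, 9% and 3% the variances are 0.354, 0.225 and 0.079, averaging 0.219. The A–C difference is 1.5 × 0.12 = 0.18.
2. Time-specific SE = √(2 × 0.219/84) = 0.072.
3. Stated model: mean variance (1.43 + 1.35 + 0.80 + 0.22)/4 = 0.95, so SE = √(2 × 0.95/84) = 0.150, about 2.1 times too large.
4. With a Tukey critical value of 2.358, the stated model needs a difference above 2.358 × 0.150 = 0.354. The true sampling SD of A–C is √((0.354 + 0.079)/84) = 0.072. Since (0.354 − 0.18)/0.072 = 2.42, power is about 1%. With the 72 h variance the threshold is 2.358 × 0.072 = 0.170, just below 0.18, so power is a little over one half.

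**Simulation (4,000–6,000 runs).** Power for A versus C at 72 h, stated model / time-specific variance:

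| Pattern | Variance 6/24/48 h | Stated SE, 15 v 3 (own 0.072) | 15% v 3% | 25% v 5% | 40% v 15% | 60% v 30% |
|---|---|---|---|---|---|---|
| Marked | 1.43/1.35/0.80 | 0.150 | 1/57% | 25/86% | 52/82% | 70/86% |
| Mild | 1.00/0.71/0.46 | 0.119 | 8/56% | 57/86% | 74/82% | 86/86% |
| Very mild | 0.54/0.39/0.25 | 0.091 | 30/56% | 81/86% | 88/83% | 93/85% |
| Dense 50% | 0.84/1.59/1.36 | 0.154 | 1/57% | 21/86% | 50/83% | 70/86% |
| Dense 60% | 0.80/1.64/1.36 | 0.155 | 1/58% | 21/86% | 48/83% | not run |
| Dense 80% | 0.33/1.64/1.75 | 0.153 | 1/57% | 23/86% | 50/82% | 70/85% |

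**False positives.** With no arm difference and r = 5% throughout, the 72 h variance is 0.13. In the marked pattern the pooled variance is (1.43 + 1.35 + 0.80 + 0.13)/4 = 0.93. At 6 h the SE is then too small by a factor √(1.43/0.93) = 1.24, and the nominal 2.358 acts like 2.358/1.24 = 1.90. Simulated family-wise error under the stated model:

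| Pattern | 6 h | 24 h | 48 h | 72 h |
|---|---|---|---|---|
| Marked | 15% | 13% | 3% | 0% |
| Mild | 18% | 9% | 2% | 0% |
| Very mild | 16% | 7% | 2% | 0% |
| Dense 50% | 3% | 16% | 11% | 0% |
| Dense 60% | 2% | 16% | 11% | 0% |
| Dense 80% | 0% | 16% | 18% | 0% |

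Time-specific variances give 4–5% throughout. Across repeat runs and correlations of 0.3 or 0.7, the peak error stays within 13–20% and power for 15% versus 3% is essentially unchanged.

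**Separate check with other distributions.** For 12% versus 2%, power was 0–40% under the stated model against 47–55% with a time-specific variance, in every profile tried. The stated model did better (68–73% against 64–66%) only for 20% versus 5% with deeper residual grades and little earlier spread.

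**The case against.** - **The text may not fix the residual.** A random intercept describes the between-patient part. A heterogeneous residual can sit beside it, the MMRM label hints at one, and an unseen analysis plan might specify it. This is possible, but it would add to the article's wording. Someone following that wording would fit equal variances.
- **Equal arms until 72 h is a favourable assumption.** A dose effect strong enough to give 15% versus 3% would normally show earlier. With the same latent shift at all times, the stated model finds A versus C at 24 or 48 h in 96–100% of trials. With half the shift before 72 h, it finds a difference at 6, 24 or 48 h in 72–91%. This stands: the motor effect as a whole would often be seen. The 72 h contrast is still usually missed, and the inflated error is untouched.
- **72 h is not singled out or powered.** That is correct. Even with the right variance, 15% versus 3% is missed about 43% of the time.
- **Direction and size are unknown.** This too is correct, and the grid includes reversals. The weakness check is also only modest support, since it tests deltoid and biceps at 15 minutes whereas MBS grades elbow and wrist flexion hours later.
- **Residual weakness may be visible in descriptive tables.** It may, but the formal comparison would still mislead.

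**Conclusion.** The point holds as a conditional, low-cost improvement. If grades are near the ceiling by 72 h and residual block is uncommon (15% versus 3%), the stated model inflates the 72 h standard error 1.3 to 2.2 times and cuts power from 56–58% to 1–30%. Family-wise error at the time of widest spread is 13–20% where 5% is intended. Both results rest on assumed grade distributions. The power result also assumes arms equal before 72 h, and the loss shrinks or reverses when residual block at 72 h is common.

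The consequence is bounded: "For the trial to be declared positive regarding the primary hypothesis, both co-primary endpoints must reach statistical significance", and those endpoints are 48 h NRS and 0–48 h MME. What is at risk is the motor half of the dose recommendation, not the declaration of a positive trial.

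**What to change.** For MBS and Bromage, replace the random intercept with an unstructured or heterogeneous covariance that has a separate variance at each time. Heterogeneous compound symmetry, tried in four of the patterns (1,200 runs), gave 55–57% power for 15% versus 3% and null errors of 2–7%. State a fallback: if the model does not converge because nearly everyone is at grade 4 at 72 h, compare the proportion with MBS below 4 at 72 h by arm, adjusted over the three pairs.

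The cost is one line of wording and a few more covariance parameters; no new data are needed. Zero variance at 72 h is a practical risk only if almost nobody is still blocked. The chance that all 252 patients (3 × 84) are at grade 4 is 0.99^252 = 8% at an overall rate of 1%, and 0.98^252 = 0.6% at 2%. The change should be fixed before unblinding.

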### Data collection

Table 3 outlines the schedule of enrolment, interventions and data measurements in accordance with the SPIRIT guidelines. Demographic data, ASA status, comorbidities, preoperative medications and the age-adjusted Charlson Comorbidity Index (aCCI) are scheduled to be collected prior to anaesthesia. Surgical, anaesthesia and perioperative data, including hemodynamic events, will be documented *via* an electronic system.

**Table 3. t0003:** Schedule of patient enrolment, study interventions, and outcome assessment according to SPIRIT statement.

			Study period				
Timepoint	Enrollment Preoperative visit	Allocation Before surgery	Post-allocation				
			Pre-anesthesia room	6 h	24 h	48 h	72 h
Enrollment							
Inclusion criteria	×						
Exclusion criteria	×						
Written informed consent	×						
Baseline data	×						
Randomization		×					
Allocation		×					
Study interventions							
Group A			**×**				
Group B			**×**				
Group C			**×**				
Outcome assesment							
NRS score				**×**	**×**	**×**	**×**
MME						**×**	
MBS score				**×**	**×**	**×**	**×**
Bromage score				**×**	**×**	**×**	**×**
ASES score				**×**	**×**	**×**	**×**
QoR-15 score					**×**	**×**	

To minimize reporting errors in the study, only investigators who will be blinded to the study design and group assignment will conduct the postoperative follow-up, which will include assessments of postoperative pain and motor block. Outcome measures will be documented and evaluated in accordance with the procedures outlined in the blinded section. An independent Data Monitoring Committee (DMC), composed of an attending orthopaedic surgeon, an attending anaesthesiologist, a pharmacist and a statistician, will oversee the conduct of the study.

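### The adjusted regression includes surgical duration, which is observed after treatment, and a baseline NRS with no named measurement, while the primary models name no baseline covariates

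*Protocol article*

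**What the plan says.** All references are to the Protocol article.

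- **Adjusted analysis** (Statistical analysis): a multivariable linear regression is to adjust for possible confounders, "including age, sex, body mass index (BMI), baseline NRS score and surgical duration". The article does not say whether this regression is primary, supportive or a sensitivity analysis.
- **Repeated measures** (same section): a mixed model "with fixed effects including group, time point and the group × time interaction, patient as a random intercept", with Tukey-adjusted pairwise comparisons.
- **Single time points** (same section): "normally distributed continuous variables will be compared using one-way ANOVA, followed by post‑hoc pairwise comparisons with Tukey’s correction", or Kruskal-Wallis if the variable is not normally distributed.
- **Success rule** (same section): at least one pair of groups must differ on both co-primary endpoints "after applying Tukey’s correction for multiple comparisons within each endpoint".
- **Baseline data** (Data collection): "Demographic data, ASA status, comorbidities, preoperative medications and the age-adjusted Charlson Comorbidity Index (aCCI) are scheduled to be collected prior to anaesthesia". Table 3 also has a generic baseline-data row marked at the preoperative visit, with no contents listed. Its NRS row is marked at 6, 24, 48 and 72 h only.
- **NRS times** (Primary and secondary outcomes): 48 h as co-primary, and "Rest pain NRS scores at 6 h, 24 h and 72 h post‑surgery" as secondary. No preoperative score is defined.
- **Timing of the intervention** (Study interventions): "A single ultrasound-guided STB will be administered in the pre-anaesthesia room 1 hour preoperatively". Table 3 places randomisation and allocation before that.

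**The concern.** Three parts of the adjustment plan do not fit together.

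1. Surgical duration is treated as a confounder, yet its value is known only after the allocated dose has been given. A post-treatment variable cannot confound a randomised comparison. If dose affected it, conditioning on it would distort the dose contrast.
2. A named covariate has no named measurement. A statistical analysis plan can settle how a model is written, but it cannot supply a preoperative pain score that was never taken.
3. Covariates appear only in a separate regression justified by confounding. Randomisation already deals with confounding in expectation. What prognostic baseline covariates offer is precision, and the comparisons that decide success do not name any.

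The precision matters most for the adjacent doses. The article chose 44 mg to find the balance between analgesia and motor function, so A–B and B–C bear directly on the stated aim.

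**Working it through.** **Timing of the covariates**

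| Covariate | Fixed before allocation? | Named in the collection schedule? |
|---|---|---|
| Age, sex | Yes | Yes (demographic data) |
| BMI | Yes | Not by name; plausibly demographic data |
| Baseline NRS | Yes, if taken | No; at most within the generic baseline-data row |
| Surgical duration | No; follows allocation and the block | Recorded with surgical data |

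Only surgical duration fails on timing. Only baseline NRS lacks a clear place in the schedule.

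**The plan's own sample size**

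Inputs (Sample size estimation): pain rates of 15%, 25% and 35%, two-sided α = 0.05, power 0.80, 84 per group, 10% dropout.

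- A versus C (15% v 35%), two proportions with continuity correction: 83 per group, close to the stated 84. Without the correction it is 73.
- Dropout: 84 / 0.90 = 93.3, rounded up to 94; 3 × 94 = 282. This reproduces.

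This point disputes no stated sample-size figure. The 84 is used below as the evaluable number per group.

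**Gain in precision from baseline covariates**

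The article gives no correlation r between covariates and outcome, so r = 0.1 to 0.5 is an assumption. Adjustment multiplies residual variance by (1 − r²). The number needed for the same precision is 84 × (1 − r²), rounded up.

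| r | 1 − r² | Fall in variance | Number giving the precision of 84 |
|---|---|---|---|
| 0.1 | 0.99 | 1% | 84 |
| 0.2 | 0.96 | 4% | 81 |
| 0.3 | 0.91 | 9% | 77 |
| 0.4 | 0.84 | 16% | 71 |
| 0.5 | 0.75 | 25% | 63 |

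**Power for the pain score**

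The article gives pain rates but no NRS means or SD. A second assumption is therefore needed: a latent normal score with equal variance, cut at one threshold. The standardised differences are then differences of normal quantiles.

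- A–B: z(0.25) − z(0.15) = −0.674 + 1.036 = 0.362
- B–C: z(0.35) − z(0.25) = −0.385 + 0.674 = 0.289
- A–C: 0.362 + 0.289 = 0.651

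The Tukey critical value for three groups with 3 × 84 − 3 = 249 degrees of freedom is 2.358 on the t scale. The non-centrality is d / √(1 − r²) × √(84/2). For A–B unadjusted it is 0.362 × 6.481 = 2.35, almost equal to the critical value, so power is about one half.

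| Contrast | Unadjusted | r = 0.1 | r = 0.2 | r = 0.3 | r = 0.4 | r = 0.5 |
|---|---|---|---|---|---|---|
| A–B | 49.6% | 50.1% | 51.5% | 54.1% | 58.0% | 63.7% |
| B–C | 31.6% | 31.9% | 33.0% | 34.9% | 37.9% | 42.4% |
| A–C | 96.8% | 97.0% | 97.4% | 98.0% | 98.7% | 99.4% |

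**MME**

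The planned means are 20, 35 and 50 mg with SD 12, so adjacent groups differ by 15/12 = 1.25 SD. The unadjusted non-centrality is 1.25 × 6.481 = 8.10 against 2.358. Power is essentially 100% and adjustment cannot raise it.

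**The case against.** **The covariate may well be collected.** Table 3 has a baseline-data row, its NRS row sits among the outcomes, and naming a baseline NRS presupposes that it is taken. The article also condenses a fuller protocol. This stands as far as it goes: a reader might infer that the regression cannot be fitted, and the article does not support that. It supports only that the itemised list and the NRS row omit the score. The clarification is still worth making before recruitment, because the omission could not be repaired later.

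**Unadjusted primary models are not an error.** This stands. ANOVA and the mixed model are valid under randomisation, the fixed effects are introduced in wording that is not exhaustive, and an adjusted regression is planned. The point is one of efficiency.

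**The power gain depends on assumptions and on the contrast.** This also stands. No NRS difference in SD units is planned anywhere, and no correlation is given. The success rule needs only one pair, and A–C is already near 97%. A reader might infer that the trial's chance of success is at risk; on these figures it is not.

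**Surgical duration is harmless in practice.** It enters only the adjusted regression, all groups receive general anaesthesia, and surgeons are blinded to dose. A reader might infer that the dose estimates will be biased; nothing in the article shows this. Even so, the variable has no claim to be a confounder, and removing it costs nothing.

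**Conclusion.** The point holds as a modest and cheap correction. It does not challenge the trial's validity.

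- Surgical duration should leave the adjustment set because of its timing. No bias is demonstrated, and it may be small.
- Baseline NRS needs a named measurement before surgery. Whether it is missing or merely unlisted cannot be settled from the article.
- Moving baseline covariates into the primary models would help by an amount the article does not fix: close to nothing at r = 0.1, and up to a quarter of residual variance at r = 0.5. The benefit is confined to the adjacent-dose pain contrasts.

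The variance figures rest on the assumed correlations. The power figures rest in addition on the latent-normal conversion and 84 evaluable patients per group.

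**What to change.** 1. Add rest NRS to the pre-anaesthesia list in Data collection, and mark it at the preoperative visit in Table 3.
2. Delete surgical duration from the adjustment set. If it is of interest, report it descriptively by group.
3. Prespecify age, sex, BMI and baseline NRS as covariates in the primary mixed model for NRS and in an ANCOVA for MME. Keep Tukey-adjusted pairwise comparisons, and report the unadjusted contrasts as sensitivity. This also settles the role of the adjusted analysis.
4. For non-normal MME, Kruskal-Wallis takes no covariates. Make a covariate-adjusted model primary in that case too, and keep Kruskal-Wallis as sensitivity.

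The cost is one 0–10 question per patient and a revision of the model text, including the Kruskal-Wallis branch. The sample size need not change. The NRS item must be in place before the first patient is treated.
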